##### Data collection

Accuracy of productions will be scored in every session to track percent accuracy for each stimulus item and the number of production attempts requiring clinician cues. These measures will be used to track treatment gains and in determining if and when to change treatment targets and/or levels according to the operationalised NDP3 instructions for this study.

#### Rapid Syllable Transition Treatment (ReST)

The ReST treatment was initially manualised by the second and third author from a verbal description of ReST treatment by its developer [name], and with assistance from [name]. The first author adapted the stimuli and further operationalised the treatment to ensure experimental control in the context of this parallel RCT. The adapted manual will be used.

##### Treatment goals and stimuli

Treatment for all children will involve correctly producing selected pseudo-word stimuli. Each treatment session has two components, each with a different goal. In the Pre-Practice component, the goal is to elicit a total of five correct productions of any of the pseudo-word stimuli from the participant. Once this is achieved, treatment moves to the Practice component, where the goal is for the participant to produce the 20 pseudo-word stimuli 5 times each (n = 100), in random order, with 80% accuracy.

The pseudo-word stimuli for the programme are designed to be read and conform to phonotactic rules of real English words [63,64]. Pseudo-words will be either at a two syllable (CVCV where C = consonant and V = vowel sound) or 3 syllable (CVCVCV) level to target the level immediately above each participant’s speech skills at assessment. Twenty child-specific pseudo-words/phrases will be constructed and used for all 12 treatment sessions: 10 will have a weak-strong prosodic pattern (e.g. ‘tebor’ or ‘teborfer’) and 10 will have a strong-weak stress (e.g. ‘farbe’ or ‘farbegee’). The consonant (C) sounds in each word are individualised for each participant to ensure a) they are sounds they can produce at least 10% of the time, b) they are maximally different in terms of place and manner of articulation and voicing to increase variation and complexity and c) are not vowel-like consonants (e.g. ‘y’ or ‘l’), to facilitate later acoustic analysis. Examples of consonants which may be included are: ‘f,’ ‘b’, ‘g’, and ‘t’, ‘m’ and ‘n.’ Vowel sounds will remain consistent across participants to ensure the stress patterns remain. No double-vowels or diphthongs (e.g. ‘eye’ or ‘ay’) will be included.

##### Treatment procedure

Each session will start with the Pre-Practice component where the child’s productions of the pseudo-words are shaped so s/he experiences correct responses. For the first two sessions, the pseudo-words will be randomly presented to gain an idea of areas of difficulty for each participant. From session three to twelve, difficult pseudo-words that require more shaping by the clinician will be presented as a primary focus to ensure correct productions are experienced in Pre-Practice. Cues will include all, or a subset of, modelling, tapping and breaking words word up into parts and then putting them together again. Knowledge of performance (KP) feedback will be given for all trials (e.g. for the prosodic pattern: “Great soft then strong beat, well done” or “you said all strong beats.”). The Pre-Practice component will take most of the session in the first two sessions, but for the majority of sessions will take approximately the first 10 minutes. Once any five pseudo-words are produced correctly, the treatment session will move into the Practice component.

In the Practice component, the 20 pseudo-words will be presented orthographically (in written form), in random order for a maximum of 100 production attempts by the child. No cues will be provided. Knowledge of results (KR), or “right/wrong”, feedback will be given after a three second delay for 50% of the 100 trials based on a decreasing feedback schedule (e.g. a randomly selected 9/10 given feedback for the first ten stimuli down to 1/10 for the final ten stimuli). After each set of 20 trials, participants will be given a timed 2 minute break (e.g. to play games or be active) to facilitate attention and compliance. Once a child produces ≥80 of the 100 productions correctly in the Practice component in two consecutive sessions, therapy progresses to the next level of difficulty. For children who started with 2 syllable pseudo-words (e.g. ‘tebor’) they will move on to the related 3 syllable pseudo-words (e.g. teborfer’). For children who started with 3 syllable words they will move on to putting the 3 syllable words into carrier phrases (e.g. ‘Can I have a begarter?’ or ‘It’s his fargeber’). The Practice component will comprise the majority of each session (approximately 50 minutes) after sessions 1 and 2.

##### Data collection

In the Pre-Practice component, total correct productions will be judged perceptually. Each pseudo-word will be counted for speech sound accuracy and for production of prosodic pattern (i.e. syllable stress) and for fluency in sequencing/transitioning of sounds within the pseudo-word. This will ensure that each participant is moved to Practice only after producing five correct responses and allow identification of areas that need more shaping in Pre-Practice. In Practice, data sheets will list all 100 pseudo-words in randomised order with asterisks identifying which items are to receive KR feedback. Space will be provided for the clinician to take data on whether the production of the whole pseudo-word was judged correct and, if any aspect was incorrect, the specific sub-parameter(s) in error: speech sounds and/or prosody and/or sequencing control.

### Treatment fidelity

Treatment fidelity, that is inter-rater reliability for (a) accuracy of response transcription and (b) application of the manualised protocol in terms of provision of cues, feedback and repetitions by the clinician, will be calculated between the clinician and the first author for 10% of each treatment session. This will document whether agreement for both measures is ≥85% (the benchmark for this study). If any variations occur for any treatment session, the first author will discuss this with the clinician contemporaneously to resolve disagreements in protocol application for future sessions.

### Outcome assessment

#### Outcome assessments and measures

Two hour post-treatment assessments will be scheduled for 1 week post treatment, 1 month post-treatment (after the no-treatment period of 4 weeks) and 4 months post-treatment (after resuming the participant’s usual speech pathology services for up to 3 months). All assessments will be completed by blinded independent assessors, that is no assessor will see the same child twice. Intra-rater and inter-rater reliability will be calculated for 10% of every probe completed to ensure transcription and judgments are above 85%. If the benchmark is not met, assessors will need to re-transcribe the recordings before discussion on items of disagreement to reach consensus.

The primary outcome will be speech (articulation) and prosodic (speech melody) accuracy on the specifically designed 292 item probe [49] administered during baseline and the three post-treatment assessments. Secondary outcome measures will include a) change in percent inconsistency across three repetitions of twenty-five words on the DEAP Inconsistency subtest and b) percent phonemes correct on the Test of Polysyllables and GFTA - 2 administered only at 1 month post-treatment. The probe and all assessments will be phonetically transcribed using the International Phonetic Alphabet, except the DEAP Inconsistency subtest which will use transcription methods according to the test manual.

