**Methods/Design:**

A parallel group, fixed size randomised control trial will be conducted in Sydney, Australia to determine the efficacy of two treatments for Childhood Apraxia of Speech: 1) Rapid Syllable Transition Treatment and the 2) Nuffield Dyspraxia Programme – Third edition. Eligible children will be English speaking, aged 4–12 years with a diagnosis of suspected CAS, normal or adjusted hearing and vision, and no comprehension difficulties or other developmental diagnoses. At least 20 children will be randomised to receive one of the two treatments in parallel. Treatments will be delivered by trained and supervised speech pathology clinicians using operationalised manuals. Treatment will be administered in 1-hour sessions, 4 times per week for 3 weeks. The primary outcomes are speech sound and prosodic accuracy on a customised 292 item probe and the Diagnostic Evaluation of Articulation and Phonology inconsistency subtest administered prior to treatment and 1 week, 1 month and 4 months post-treatment. All post assessments will be completed by blinded assessors. Our hypotheses are: 1) treatment effects at 1 week post will be similar for both treatments, 2) maintenance of treatment effects at 1 and 4 months post will be greater for Rapid Syllable Transition Treatment than Nuffield Dyspraxia Programme treatment, and 3) generalisation of treatment effects to untrained related speech behaviours will be greater for Rapid Syllable Transition Treatment than Nuffield Dyspraxia Programme treatment. This protocol was approved by the Human Research Ethics Committee, University of Sydney (#12924).

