#### Eligibility assessment

All potential participants who are not excluded during telephone screening will participate in a two-hour assessment to ensure they meet the inclusion criteria and meet the diagnostic criteria for CAS. The current gold standard in CAS diagnosis is expert clinical opinion as there are no validated standardised assessments available [13]. Accordingly CAS diagnosis will be made by the first author according to the ASHA (2007) criteria [1] as well as Strand’s 10 point checklist [47] where each of the ten items are assessed across three tasks and a diagnosis of CAS is made if a child scores four or higher on the checklist. Diagnoses will be verified by the second author blinded to the first author decision.

The eligibility assessment includes a case history questionnaire, hearing screening [48], the CELF [45,46] to determine age appropriate comprehension skills, completing three repetitions within the Inconsistency subtest of the Diagnostic Evaluation of Articulation and Phonology (DEAP) [49] to determine percentage within-word consistency across 25 words, the Test of Polysyllables [50,51] to document phonemic and phonetic level errors in words with greater complexity, a 100-utterance connected speech sample [52] and an oral structural and functional examination [53].

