#### Diagnostic assessment

Eligible participants will undergo a further two hours of assessment to describe their broader communication skills. The further assessment will test memory and processing skills using the Children’s Test of Nonword Repetition [54], Comprehensive Test of Phonological Processing [55], Test of Auditory Processing Skills (3^rd^ edition) [56] (verbal memory, auditory discrimination); processing and production of prosody using the PEPS-C Test of Prosody [57]; and severity of articulation disorder using the Goldman-Fristoe Test of Articulation - Second edition (GFTA-2) [58]. Finally, an estimate of verbal cognitive ability will be obtained with the Peabody Picture Vocabulary Test – 4 [59,60] .

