#### Data analysis

Clinical effect sizes will be reported using Cohen’s d. A series of repeated measures ANOVA with between subject factor of treatment (NDP3, ReST) and within subject factor of time (pre-, 1 week post-, 1 month post-, and 4 months post-treatment) will be used to determine the relative efficacy of the two treatments as measured by the 292-item experimental probe. Separate analyses will be run for treated stimuli, to document treatment and maintenance effects, and untreated stimuli, to document generalisation of treatment effects and their maintenance. Additional repeated measures ANOVA (2 groups x 4 time points) will be run for the DEAP Inconsistency subtest [49], GFTA-2 [58] and the Test of Polysyllables [50,51]. If there is any attrition, an intention-to-treat analysis will be conducted.

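### GFTA-2 and the Test of Polysyllables have two scheduled time points, so the 2 × 4 repeated measures ANOVA specified for them cannot be run

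*Protocol article*

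**What the plan says.** Under Outcome assessments and measures, secondary outcome b) is "percent phonemes correct on the Test of Polysyllables and GFTA - 2 administered only at 1 month post-treatment".

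Each test also has one pre-treatment administration. The Eligibility assessment includes "the Test of Polysyllables [50,51] to document phonemic and phonetic level errors in words with greater complexity", and the Diagnostic assessment measures "severity of articulation disorder using the Goldman-Fristoe Test of Articulation - Second edition (GFTA-2").

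The Data analysis section then states: "Additional repeated measures ANOVA (2 groups x 4 time points) will be run for the DEAP Inconsistency subtest [49], GFTA-2 [58] and the Test of" (the quote breaks off in the name of the last instrument listed, which is the polysyllable test). The same section defines the time factor for the probe analysis as the "within subject factor of time (pre-, 1 week post-, 1 month post-, and 4 months post-treatment"), and the four time points of the additional ANOVAs can only be these.

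Two other instruments do have four occasions. The 292-item probe is "administered during baseline and the three post-treatment assessments". The abstract (Methods/Design) has the "Diagnostic Evaluation of Articulation and Phonology inconsistency subtest administered prior to treatment and 1 week, 1 month and 4 months post-treatment".

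**The concern.** The schedule and the model are both stated explicitly, in adjacent sections, and they cannot both be carried out for GFTA-2 and the Test of Polysyllables. A four-level time factor needs data at 1 week and 4 months, and neither test is planned at those visits.

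As written, two named secondary outcomes have no executable analysis. Three replacements are plausible: a comparison of 1-month scores alone, a change-score (2 × 2) analysis, or a baseline-adjusted comparison. In a trial of about 20 children these can give noticeably different results, so the choice should be on record before the data are seen. A reader of the analysis section would also expect evidence on immediate gain and 4-month maintenance from these tests, which the schedule cannot supply.

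**Working it through.** **1. Count the scheduled occasions per instrument.**

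| Instrument | Pre | 1 week | 1 month | 4 months | Total |
|---|---|---|---|---|---|
| 292-item probe | yes | yes | yes | yes | 4 |
| DEAP Inconsistency | yes | yes | yes | yes | 4 |
| Test of Polysyllables | yes (eligibility) | no | yes | no | 2 |
| GFTA-2 | yes (diagnostic) | no | yes | no | 2 |

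The plan's own figure of 4 time points is reproduced for the probe and DEAP. It is not reproduced for the other two tests.

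**2. Compare with what the model needs.** A 2 × 4 design has 2 × 4 = 8 cell means. The rank of the group-by-time design matrix is 8 under the probe and DEAP schedule. Under the schedule for GFTA-2 and the Test of Polysyllables it is 2 × 2 = 4. The 1-week and 4-month cells are empty in both arms for every child, so the time effect and the interaction at those levels are not estimable.

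**3. Degrees of freedom with N = 20 (10 per group, Methods and design).** With T time points and 2 groups, the group-by-time test has (2 − 1)(T − 1) and (N − 2)(T − 1) degrees of freedom.
- T = 4, as specified: 3 and 18 × 3 = 54.
- T = 2, as scheduled: 1 and 18 × 1 = 18.

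**4. Compare the two executable two-time-point analyses.** With equal variances before and after treatment and pre–post correlation ρ, the variance of the arm difference is proportional to 2(1 − ρ) for change scores (the 2 × 2 interaction) and to 1 − ρ² for ANCOVA. The large-sample ratio of ANCOVA to change score is therefore (1 − ρ²) / [2(1 − ρ)] = (1 + ρ)/2. Estimating the covariate slope inflates the ANCOVA variance by about 1 + 1/(2n − 4) for a normal covariate. At n = 10 per group this is 1 + 1/16 = 1.0625.

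| Assumed ρ | (1 + ρ)/2 | × 1.0625 | Variance reduction |
|---|---|---|---|
| 0.5 | 0.75 | 0.80 | about 20% |
| 0.7 | 0.85 | 0.90 | about 10% |
| 0.9 | 0.95 | 1.01 | none |

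The documents give no pre–post correlation for either test, so these values of ρ are assumptions. The table bears only on the choice of replacement; it does not measure the size of the inconsistency.

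**The case against.** The best reply is that this is loose wording about two secondary measures. Hypotheses on gain, maintenance and generalisation are to be tested on the probe, which has all four occasions. The mismatch is visible before any child is assessed, and the stated method shrinks naturally to a 2 × 2 ANOVA, which is valid in a randomised trial. All of this is fair and limits the weight of the point. It does not remove the contradiction, because the text names a four-level analysis for tests with two levels.

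Three ways of explaining the conflict away do not work.
- The restriction to 1 month could grammatically attach to GFTA-2 alone. The natural reading covers both tests. Even on the narrow reading GFTA-2 still conflicts, and no section gives the Test of Polysyllables another post-treatment occasion.
- The intention-to-treat sentence in Data analysis applies if there is attrition. The missing cells here were never scheduled.
- Condensation into a journal article does not explain it, since the article states both the schedule and the model.

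Some stronger readings are tempting, and the documents do not support them.
- A reader might infer that the main treatment comparison is compromised. It is not: the probe and DEAP schedules fit the 2 × 4 model. The article lists DEAP as primary in the abstract and secondary in the outcome section, but that does not affect this point.
- A reader might infer that these two tests say nothing about maintenance. The 1-month visit follows a 4-week period without treatment, and hypothesis 2 covers 1 month as well as 4 months, so a between-arm comparison at 1 month does bear on retention.
- A reader might infer that a data-driven choice of analysis is unavoidable. It is a risk only if the text is left uncorrected.

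**Conclusion.** The point stands as an internal contradiction confined to two secondary outcomes. Half of the time levels (2 of 4) specified for GFTA-2 and the Test of Polysyllables have no scheduled data, so the stated ANOVA cannot be fitted to them. What is lost on these tests is 1-week gain, the separation of initial gain from retention, and 4-month maintenance.

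This conclusion rests only on the article's own schedule and needs no numerical assumption. The preference for baseline adjustment over a 2 × 2 ANOVA is weaker. It assumes equal variances, a roughly normal covariate and a moderate correlation, and it disappears near ρ = 0.9.

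**What to change.** Reconcile the outcome section and the Data analysis section before any outcome data are seen.

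- **If the 1-month restriction is what was intended:** in Data analysis, keep the 2 × 4 repeated measures ANOVA for the 292-item probe and for the DEAP Inconsistency subtest. For GFTA-2 and the Test of Polysyllables, specify a two-time-point analysis. The preferred form is an ANCOVA of the 1-month score on treatment with the pre-treatment score as covariate, reported as an adjusted difference with 95% CI. A 2 × 2 repeated measures ANOVA is an acceptable alternative if the team wishes to keep its stated method. Claims from these tests should be limited to the 1-month comparison.
- **If four time points were intended:** change the outcome section to schedule both tests at 1 week and 4 months, and leave the 2 × 4 model in place.

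The first route costs about one sentence and no new testing, because both tests are already given before treatment. It assumes that the pre-treatment recordings are scored as percent phonemes correct in the same way as the 1-month ones, which is worth stating. The second route adds two administrations of each test per child to the post-treatment visits, which are planned at two hours each.

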#### Data analysis

Clinical effect sizes will be reported using Cohen’s d. A series of repeated measures ANOVA with between subject factor of treatment (NDP3, ReST) and within subject factor of time (pre-, 1 week post-, 1 month post-, and 4 months post-treatment) will be used to determine the relative efficacy of the two treatments as measured by the 292-item experimental probe. Separate analyses will be run for treated stimuli, to document treatment and maintenance effects, and untreated stimuli, to document generalisation of treatment effects and their maintenance. Additional repeated measures ANOVA (2 groups x 4 time points) will be run for the DEAP Inconsistency subtest [49], GFTA-2 [58] and the Test of Polysyllables [50,51]. If there is any attrition, an intention-to-treat analysis will be conducted.

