Based on these foundational studies, we are well poised to conduct a larger scale clinical trial of ReST treatment against NDP3. Our hypotheses for this planned randomised control trial are: 1) treatment gains from pre-treatment to 1 week post-treatment will be similar for both treatments, 2) ReST treatment will result in greater maintenance of treatment effects at 1 and 4 months post-treatment than NDP3 treatment, and 3) ReST treatment will result in greater generalisation of treatment effects to untrained but related speech behaviours at 1 week, 1 month and 4 months post-treatment than NDP3 treatment.

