## Methods and design

A parallel group, fixed size randomised control trial will be conducted in Sydney, Australia to determine the comparative efficacy of two treatments for Childhood Apraxia of Speech: the Rapid Syllable Transition Treatment (ReST) and the Nuffield Dyspraxia Programme – Third edition (NDP3). This protocol has been approved by the Human Research Ethics Committee of the University of Sydney (approval number 12924).

A power calculation has been used to determine the number of participants to be recruited. Previous pre and post treatment data from within-subject ReST studies (e.g. [12,16]) for a total number of 14 participants demonstrated statistically significant differences for 12 of the 14 participants and large effect sizes (Cohen’s d = 1.36). Based on this, the estimated sample size to detect a reliable treatment effect (alpha level 0.05, beta level 80%) is 6 per group for this RCT. We have no estimates for the NDP3 due to lack of published effect sizes or data to enable calculation of an effect size. On this basis we propose 10 per group to allow for attrition and to accommodate the higher heterogeneity with a between-subjects design.

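### The four-visit repeated measures ANOVA is not reconciled with the intention-to-treat promise, and using the pre-treatment score as an outcome level gives up precision that a covariate would recover at no cost in data

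*Protocol article*

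**What the plan says.** Under Data analysis, the protocol article commits the probe to "A series of repeated measures ANOVA with between subject factor of treatment (NDP3, ReST)" and a "within subject factor of time (pre-, 1 week post-, 1 month post-, and 4 months post-treatment)". Treated and untreated stimuli are analysed separately. The pre-treatment score is therefore one of four responses, not a covariate. The section does not say which term of the ANOVA decides the comparison. It closes with "If there is any attrition, an intention-to-treat analysis will be conducted" and names no method for missing scores.

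The same model is extended to secondary measures: "Additional repeated measures ANOVA (2 groups x 4 time points) will be run for the DEAP Inconsistency subtest", and also for the GFTA-2 and the Test of Polysyllables. The Outcome assessments and measures section, however, appears to give those last two after treatment at 1 month only.

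The sample size paragraph under Methods and design starts from "large effect sizes (Cohen’s d = 1.36)" in within-subject ReST data, and concludes "the estimated sample size to detect a reliable treatment effect (alpha level 0.05, beta level 80%) is 6 per group for this RCT". It then says "On this basis we propose 10 per group to allow for attrition and to accommodate the higher heterogeneity with a between-subjects design". Attrition is thus expected, but no rate is given.

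**The concern.** A conventional repeated measures ANOVA works on complete rows. A child who attends at 1 week and 1 month but misses 4 months contributes nothing unless the missing score is filled in or a likelihood-based model is used instead. The article fixes the ANOVA and promises intention-to-treat, but does not say how the one delivers the other. Intention-to-treat settles who is analysed and in which arm. It does not handle missing scores, and it should not depend on whether anyone drops out.

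At about 10 children per arm, discarding scores already collected is costly. It can also bias the comparison if the children who miss a late visit differ from those who attend. The 4-month visit, on which the maintenance hypothesis partly rests, follows up to 3 months back in the child's usual services, so missed visits there are plausible.

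The second issue is efficiency. With baseline as a level of time, the treatment-by-time contrast from baseline to a visit is a comparison of change scores. The treatment main effect averages in a time point at which no treatment effect can exist. Using the same baseline score as a covariate gives a more precise arm difference.

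**Working it through.** **Inputs.** From the document: d = 1.36, alpha 0.05, power 80%, 6 per group calculated, 10 per group planned, three follow-ups. Not in the document and therefore assumed: the share p of children missing each follow-up (3% to 15%, independent between visits) and the pre-post correlation rho (0.3 to 0.9).

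**The plan's own figure.** A paired, two-sided t-test at d = 1.36 needs 6.4 children, so 7 rounded up (power at 6 is 76%). This is close to the stated 6. A two-sided, two-sample t-test at the same d needs 9.5, so 10 per arm. The stated 6 thus comes close as a within-subject figure but not as a two-sided between-arm one. That is a separate matter. It is relevant here only because 10 per arm leaves almost no slack at this d.

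**Complete cases.** The share with all three follow-ups is (1 − p)^3. The share of observed follow-up scores thrown away is 1 − (1 − p)^2.

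| p per visit | (1 − p)^3 | Completers of 20 | Observed follow-up scores discarded |
|---|---|---|---|
| 3% | 0.913 | 18.3 | 6% |
| 5% | 0.857 | 17.1 | 10% |
| 10% | 0.729 | 14.6 | 19% |
| 15% | 0.614 | 12.3 | 28% |

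**Power by number per arm** (two-sided, two-sample t, d = 1.36 taken as a between-arm effect): 82% at 10, 77% at 9, 72% at 8, 65% at 7, 57% at 6.

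At p = 10% there are 14.6 / 2 = 7.3 completers per arm, so about 7 and 65%. Using all available visits, 10 x 0.9 = 9 per arm are observed at any one visit, and power is about 77%. The cost of requiring complete rows is therefore roughly 77 − 65 = 12 percentage points in this case.

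**Baseline as response or covariate.** For one follow-up visit with unit variances, the change score has variance 2(1 − rho). Adjustment for baseline leaves 1 − rho^2 = (1 − rho)(1 + rho). The ratio is (1 + rho)/2. Simulated power at 10 per arm, for a true difference of 1 SD with no missing data:

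| rho | Variance ratio | Change score | Baseline as covariate |
|---|---|---|---|
| 0.3 | 0.65 | about 42% | about 57% |
| 0.5 | 0.75 | about 56% | about 66% |
| 0.7 | 0.85 | about 78% | about 81% |
| 0.9 | 0.95 | above 99% | above 99% |

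With no true difference, both analyses rejected in about 5% of simulated trials. The difference between them is one of efficiency, not validity.

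**The case against.** Several stronger readings are tempting, and the document does not support them.

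- *The ANOVA contradicts intention-to-treat, or drops every child with a missed visit.* A reader might infer this, but the text never says such children are excluded. Its one sentence on attrition points the other way. ANOVA on imputed data would satisfy intention-to-treat, and the missing-data method may stand in a full protocol or analysis plan that is not shown. What remains is that the two fixed statements are not joined, and that the intention-to-treat sentence is wrongly conditional.
- *Baseline as a level of time is an error.* It is not. The hypotheses are worded as gains ("treatment gains from pre-treatment to 1 week post-treatment will be similar for both treatments"), and the treatment-by-time contrast addresses gains validly under randomisation. Dilution of the main effect matters only if the main effect is the test, which the text does not say.
- *Missed visits cut power from 82% to 65%.* This compares 7 completers per arm with a trial that has no missing scores. No analysis recovers scores never observed, so the fair comparator at 10% missing is about 77%.
- *27% of children are lost* (1 − 0.729). That is one assumed rate with independent misses. If misses are mainly permanent drop-out they overlap, and 10% missing at 4 months then loses about 10% of children.

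Two further points stand. Twenty is the minimum: the article allows up to 30, and at 10% missing per visit 30 x 0.729 = 21.9 completers would still exceed 20. And d = 1.36 is a within-subject ReST effect, so the power figures for a between-arm comparison are illustrative. Also, wide variation in age and severity may well make rho high, where the covariate gains little.

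**Conclusion.** The point holds as a gap between two stated elements of the analysis and as an available gain in precision. It does not show that the plan is invalid. If the ANOVA is run on complete rows, the loss ranges from about 2 to about 8 of 20 children over assumed miss rates of 3% to 15% per visit, and is smaller if misses overlap. At 10% per visit the avoidable loss of power is about 12 points at d = 1.36. The covariate gains about 15 points of power at rho 0.3, 10 at 0.5, 3 at 0.7 and nothing at 0.9, for a 1 SD difference at 10 per arm. All of this rests on assumed miss rates and correlations, because the document gives neither. The change is worth making because the baseline probe is already collected and the trial is small.

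**What to change.** Delete the condition on attrition and state that all randomised children are analysed in the arm to which they were allocated.

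For the probe (treated and untreated sets separately), and for any other measure taken at all three follow-ups, replace the 2 x 4 ANOVA with a linear mixed model. Fit it by REML with Kenward-Roger degrees of freedom to the 1-week, 1-month and 4-month scores, with treatment, time, treatment x time and the pre-treatment score as covariate, using all available visits. Report the arm difference at each visit with a 95% confidence interval. The model relies on missing scores being explained by the observed ones, and the plan should say so.

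This three-visit model does not fit the GFTA-2 and the Test of Polysyllables if they are given after treatment only at 1 month. The Outcome assessments and measures section and the four time points under Data analysis must be reconciled for these two. If they are given only at 1 month, use ANCOVA on the 1-month score adjusted for the pre-treatment score.

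The cost is a change of wording and slightly more analysis work. No new data are needed.
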